#### Sample Size and Power Considerations

The sample size was chosen to ensure adequate power in order to examine the efficacy of tobacco-specific biomarker feedback in terms of the difference of SHS home exposure (primary outcome) between the two treatment groups at week 26. The power calculation was based on two-sided, two-sample *t* test assuming a type I error of 0.05. A total sample size of 180 (90 per treatment group) was determined to achieve 85% power in order to detect an expected difference (between 1.15 [SD 1.58] μg/m^3^ for the biomarker feedback group and 1.89 [SD 1.68] μg/m^3^ for the health education group) in air nicotine levels measured by dosimeters, which was derived from the assumed adoption rates of home smoking bans of the two treatment groups (55% vs 25%).

### Statistical Analysis

#### Primary Analyses

For the continuous end points such as reduction (ie, change score) in SHS home exposure (primary outcome), child urinary cotinine levels (secondary outcome), and parental self-report amount of smoking, the primary analysis will be the two-sided *t* tests for the measurements at week 26. In case the distribution of nicotine or cotinine level shows nonnormality, the logarithm transformation on the biomarkers or nonparametric Wilcoxon rank sum test will be applied. Categorical variables such as the adoption of home smoking restriction policies and parental quitting behaviors will be analyzed using a Chi-square test (or the Fisher exact test if there are cells with a frequency ≤ 5).

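### The 85% power was calculated for week-26 nicotine levels and is not shown to apply to the unadjusted change-score t test named as primary; adjusting for baseline would secure it at any correlation

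*Protocol article*

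**What the plan says.** All references are to the protocol article.

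- **Sample Size and Power Considerations.** The calculation uses a two-sided t test at the 5% level, and its result is stated as "A total sample size of 180 (90 per treatment group) was determined to achieve 85% power". The intervention arm enters as "between 1.15 [SD 1.58] μg/m^3^ for the biomarker feedback group"; the control arm enters with mean 1.89 and SD 1.68. These are air nicotine levels at week 26. The origin of the difference is explained by the clause "which was derived from the assumed adoption rates of home smoking bans of the two treatment groups (55% vs 25" (percentages of homes).
- **Primary and Secondary Outcomes.** The primary outcome is the change in home exposure on the dosimeter at 26 weeks.
- **Primary Analyses.** The primary test is an unadjusted two-sided t test: "For the continuous end points such as reduction (ie, change score) in SHS home exposure (primary outcome"). The same sentence then speaks of the week-26 measurements, so its wording mixes the two scales.
- **Missing Data Analyses.** A participant without a week-26 value is given a change of zero. That rule only makes sense if change is what is analysed.
- **Secondary Analyses.** Covariate-adjusted regressions and mixed models are supportive. Baseline air nicotine is not among the covariates given as examples.

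**The concern.** The article states both the basis of the power calculation and the primary test, and the two are on different scales. Subtracting baseline removes between-home variation only if baseline predicts follow-up well enough. Otherwise it adds baseline noise. The sample-size assumption makes this a live question: a home that adopts a ban is taken to end close to zero wherever it began, so in those homes subtracting baseline only adds variance.

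A null result from the declared test would naturally be read as coming from an 85%-powered comparison. The article does not show that it was one.

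**Working it through.** **1. Reproduce the stated figure.** Difference = 1.89 − 1.15 = 0.74. Pooled SD = √[(1.58² + 1.68²)/2] = 1.631. Standard error at 90 per arm = 1.631 × √(2/90) = 0.243. Noncentrality = 0.74/0.243 = 3.04. The noncentral t with 178 df gives **85.7%**, against 85% stated. The figure is correct for week-26 levels with complete data.

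**2. What a change score needs.** Randomization makes the expected baseline means equal, so the expected difference in change is still 0.74. The SD becomes

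SD²(change) = SDy² + SDx² − 2·ρ·SDx·SDy,

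where x is baseline, y is week 26 and ρ is their correlation. For analysis of covariance (ANCOVA) the residual variance is SDy²(1 − ρ²). The change score has less power than the level comparison when ρ < SDx/(2·SDy), which is 0.5 at equal SDs. The article gives no SDx, ρ or SD of change, so both models below rest on assumptions.

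**3. Equal-SD model (assumed SDx = SDy = 1.631; 90 per arm).**

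| ρ | SD of change | Power, change score | Power, ANCOVA |
|---|---|---|---|
| 0 | 2.31 | 57% | 86% |
| 0.3 | 1.93 | 73% | 89% |
| 0.5 | 1.63 | 86% (break-even) | 94% |
| 0.6 | 1.46 | 92% | 97% |
| 0.7 | 1.26 | 97% | 99% |

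At ρ = 0.3 the change score would need 123 per arm for 85% power.

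**4. Ban-adoption model.** Let a and b be the mean levels in homes with and without a ban.

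- Means: 1.15 = 0.55a + 0.45b and 1.89 = 0.25a + 0.75b. So b − a = 0.74/0.30 = 2.467, b = 2.507 and a = 0.04.
- Variances: subtracting the between-group part p(1 − p) × 2.467² from 1.58² and 1.68² and solving gives 2.26 for non-ban homes (SD about 1.50) and −0.05 for ban homes, which is zero within rounding.

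This solution supports reading 1.58 and 1.68 as SDs of levels.

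Now assume that every home is unrestricted at baseline (SD 1.5), that adoption is unrelated to the baseline level, and that r is the correlation over time in homes that do not adopt a ban. With adoption proportion p,

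Var(change) = p·2.25 + (1 − p)·2·2.25·(1 − r) + p(1 − p)·2.467².

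At r = 0.5 this is 3.756 for p = 0.55 (SD 1.94) and 3.391 for p = 0.25 (SD 1.84). The standard error is √[(3.756 + 3.391)/90] = 0.282, the noncentrality is 0.74/0.282 = 2.63, and power is 74%.

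| r | Power, change score | Power, ANCOVA (common slope 0.60r) |
|---|---|---|
| 0 | 60% | 86% |
| 0.3 | 68% | 86% |
| 0.5 | 74% | 88% |
| 0.7 | 81% | 90% |
| 0.8 | 84% | 92% |
| 0.83 | 85% (break-even) | 92% |
| 0.9 | 88% | 93% |
| 1.0 | 91% | 95% |

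Break-even comes from setting the summed change variances equal to the summed level variances: r = 1/(0.75 + 0.45) = 0.83. Simulated ANCOVA agrees with the formula to within about one percentage point (87% at r = 0.5).

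**The case against.** **The stronger reading.** A reader might infer that the change-score test has less power than planned on the article's own inputs. The documents do not support that, because the quantities that decide it are absent. Above ρ = 0.5 in the equal-SD model, or r = 0.83 in the ban-adoption model, the declared test has more power than planned.

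**Homes already restricted.** The ban-adoption model assumes none at baseline. Under Participants, enrollees did not have to report smoking at home, and the dosimeter needed only to exceed 0.02 μg/m³, which the implied ban-home level of 0.04 does. Suppose a fraction q already has a ban and keeps it, with 55% and 25% read as week-26 prevalence (an assumption). Change-score power at r = 0.5 and 0.7 is then 79% and 86% for q = 0.10, 86% and 93% for q = 0.20, and 90% and 96% for q = 0.25. This objection stands: any shortfall could shrink or reverse.

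**Enrolment exceeded the target.** With the 98 and 97 randomized and complete data, the level comparison has 88% power. The change score in the ban-adoption model has 78%, 84% and 87% at r = 0.5, 0.7 and 0.8. This narrows the gap but does not settle it.

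**Baseline is used elsewhere, and the test is valid.** The supportive mixed models use all three time points, but they are not the primary analysis. An unadjusted change-score t test is unbiased under randomization, so this is a matter of efficiency and reporting.

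**Analyses are complete.** The Abstract and Results say so. A silent switch of the primary analysis would be a post hoc change, and this governs the form of the fix.

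**Conclusion.** The mismatch stands. The 85% describes a t test of week-26 levels, while the Outcomes, Primary Analyses and Missing Data sections make an unadjusted change score primary. Power for the declared test is about 57% to 97% for correlations from 0 to 0.7 in the equal-SD model, and about 60% to 91% for r from 0 to 1 in the ban-adoption model. ANCOVA stays at about 86% or more in both, so its advantage does not depend on the unknown correlation.

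These figures assume 90 per arm, complete data and the raw scale. They ignore skewness, the log or Wilcoxon fallback, and zero-change imputation, which would dilute the difference. Severity is moderate: there is no bias, but the quoted power is attached to a different analysis.

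**What to change.** 1. Estimate the primary comparison as week-26 home nicotine on treatment with baseline home nicotine as covariate, on the log scale if the article's nonnormality provision applies. Do the same for child cotinine and cigarettes per day.
2. Because analyses are reported complete, keep the declared change-score test and present the adjusted result beside it, labelled as a later change.
3. In Primary Analyses, say plainly that the declared test is on change, and remove the ambiguity about week-26 measurements.
4. In Sample Size, state that the 85% refers to week-26 levels with complete data, and give power for the analysis used over a range of correlations.
5. State how missing values enter the adjusted model. The existing zero-change rule amounts to setting the week-26 value equal to baseline, so it can be carried over unchanged.

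The cost is a few sentences and one extra model per outcome. No new data are needed: a baseline dosimeter value above the detection limit and a baseline child urine sample were conditions of eligibility. The real cost is that the adjusted analysis was not the declared one, so it must be disclosed as a later change.

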To determine positive smoking status, participants were asked to provide a urine sample at the baseline visit, which was tested using a NicAlert (Nymox Pharmaceutical Corporation, Quebec, Canada) test strip (a semiquantitative determination of cotinine levels in urine). Individuals with cotinine levels of >10 ng/mL on the NicAlert were verified as active smokers and eligible for study participation. In addition, the child enrolled needed to provide a minimum of 17 mL of urine for sample analysis of nicotine, cotinine, and NNAL. These laboratory assay results were required to provide biomarker feedback to participants in the active condition. If a sufficient amount of urine was not collected at the baseline visit, multiple attempts were made for additional collection visits. The participant was marked ineligible for participation if a sample was not collected from the child within a 2-week window of the baseline visit.

Further, home smoking was verified using a nicotine dosimeter placed in the participant’s home at the baseline visit for a total of 7 days. Upon successful retrieval of the dosimeter, a participant was considered eligible for study participation if their dosimeter value was greater than the limit of detection. The limit of detection for this study was 0.02 μg/m^3^ [42].

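### The fallback for the primary test is left open between a log transformation and a Wilcoxon test, and the plan's own figures suggest the fallback will be needed

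*Protocol article*

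**What the plan says.** Under Statistical Analysis, Primary Analyses, the continuous endpoints include "reduction (ie, change score) in SHS home exposure (primary outcome"), and for these "the primary analysis will be the two-sided *t* tests for the measurements at week 26". The next sentence sets the exception: "In case the distribution of nicotine or cotinine level shows nonnormality", then "the logarithm transformation on the biomarkers or nonparametric Wilcoxon rank sum test will be applied".

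Sample Size and Power Considerations uses the raw scale: "The power calculation was based on two-sided, two-sample *t* test assuming a type I error of 0.05". It compares air nicotine levels of 1.15 (SD 1.58) μg/m³ under biomarker feedback with 1.89 (SD 1.68) μg/m³ under health education, derived from assumed home-ban rates of 55% and 25%, and concludes that "A total sample size of 180 (90 per treatment group) was determined to achieve 85% power".

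Two other places bear on the point. Participants fixes the floor of the measurement: "The limit of detection for this study was 0.02" μg/m³. Missing Data Analyses gives participants without week-26 data a change of zero.

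**The concern.** The plan states a decision rule for its primary outcome, but the rule does not lead to one test. Once non-normality is declared, two analyses are allowed and nothing picks between them. Nothing says that the choice is made without knowledge of treatment arm. The log is attached to the biomarkers and the trigger to the level, while the endpoint is a change score. So it is unclear whether the analysis would compare log levels at week 26, log ratios to baseline, or something else.

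The tests also estimate different things. The raw t test gives a difference in means in μg/m³, the log-scale t test a ratio of geometric means, and the Wilcoxon test a shift in ranks. The headline effect measure is thus not settled until the distribution is seen. If the analyst can also see results by arm at that moment, the nominal 5% no longer holds.

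**Working it through.** **1. The plan's sample size, reproduced.** Inputs from Sample Size and Power Considerations: difference 1.89 − 1.15 = 0.74; common SD √[(1.58² + 1.68²)/2] = √2.6594 = 1.631; two-sided α 0.05; power 85%.

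n per arm = 2 × 2.6594 × (1.960 + 1.036)² / 0.74² = 5.319 × 8.978 / 0.5476 ≈ 87.2, so 88. At 90 per arm the power is 86.1% (normal approximation) or 85.7% (noncentral t). The stated figures are sound for a raw-scale t test on the level.

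**2. Can the planned level be normal?** Air nicotine cannot be below zero. Under normality the share below zero is Φ(−mean/SD):

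- Feedback: Φ(−1.15/1.58) = Φ(−0.728) = 23.3%, about 21 of 90 homes.
- Control: Φ(−1.89/1.68) = Φ(−1.125) = 13.0%, about 12 of 90 homes.

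So the plan's own figures rule out a normal level, which is the quantity the trigger names.

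**3. What shape do the figures imply?** This is a derivation; the plan does not state it. Assume two kinds of home, with mean *a* under a ban and *b* without:

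- 0.55a + 0.45b = 1.15 and 0.25a + 0.75b = 1.89.
- Subtracting: 0.30(b − a) = 0.74, so b − a = 2.467, a = 0.04 and b = 2.51 μg/m³.

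Rounding of the two means alone moves *a* between 0.02 and 0.06. Solving the SDs the same way leaves no variance in ban homes (−0.05, zero within rounding) and an SD of about 1.50 in the others. The implied level is a cluster near the 0.02 detection limit plus a wide component. In simulated samples of 90 from this mixture, a Shapiro test rejected normality every time on the raw scale, and every time on the log scale at a 25% ban rate. The log would not restore normality.

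**4. The change score.** The documents give no baseline mean, SD or correlation. With an assumed baseline ban share of 0–25% and within-home correlation of 0–0.8, Shapiro rejection at n = 90 ranged from about 21% to 100%. Zero-change imputation would add a spike at zero.

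**5. Size of the consequence.** Simulated at 90 per arm from the mixture in step 3 (gamma or lognormal non-ban homes), and for the null also from plain lognormals with the plan's SD-to-mean ratios:

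| | Raw t | Wilcoxon | Log t | Smaller p, log or Wilcoxon | Smallest p of all three |
|---|---|---|---|---|---|
| Type I error, level | 4.5–5.6% | 4.9–5.6%* | 4.7–5.5% | 6.1–6.8% | 7.6–8.8% |
| Power, planned effect, level | 85% | 94% | 98% | – | – |

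*Lowest single result 4.7%, with lognormal non-ban homes and 25% bans.

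Over a wider set of assumed distributions, the two-way figure was roughly 6–9% and the three-way figure about 7–11%. Under the planned effect, the three tests did not all agree on significance in 13–14% of simulated trials.

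**The case against.** The plan does name a default, and it ties the switch to the shape of the distribution, not to p values. A normality criterion is the kind of detail an unseen analysis plan may supply. At about 90 per arm the raw t test holds its level despite skewness. All of this stands, and it limits the point.

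Four stronger readings are tempting, and the documents do not support them.

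- **That type I error is about 8–9%.** That figure takes the smallest of three p values. Once the trigger fires, only log and Wilcoxon remain, and inflation arises only if someone chooses between them with results by arm in view. The text neither says nor excludes this.
- **That the log cannot be applied.** A raw change can be zero or negative, so its log is undefined. But the text puts the log on the biomarkers, and a change in log levels is feasible. The defect is ambiguity.
- **That the primary data cannot be normal.** This is shown for the level. For the change score it is likely, not certain.
- **That the plan expects 0.04 μg/m³ in ban homes.** That value is derived from rounded inputs and a two-component assumption.

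What the objection does not remove is the unresolved alternative itself. A stated rule that ends in two different tests, on the primary outcome, is badly fixed and not merely brief.

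**Conclusion.** The point holds at moderate weight. The replacement for the primary t test is not determined, the scale of the log is unclear, and the planned levels (23% and 13% below zero if normal) mean the switch should be expected for the level. The primary effect measure is therefore unsettled until the data are seen.

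The possible cost in type I error is roughly 6–9% for log versus Wilcoxon and, at worst, about 7–11% over all three tests. Both ranges assume the distributions above and a choice made with arm results in view; neither is an expected error rate under the rule as written. Any one test fixed in advance holds about 5%. The sample size calculation is not in question.

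**What to change.** Delete the normality-triggered switch. Name one primary variable, scale and test, adjusted for baseline air nicotine, which is already collected. One sound option is ANCOVA of log week-26 air nicotine on arm and log baseline, reported as a geometric mean ratio with a 95% confidence interval. It needs a stated rule for values below 0.02 μg/m³ (for example 0.02/√2), with a left-censored model as a check. Keep the raw-scale difference and the Wilcoxon test as labelled sensitivity analyses, settle cotinine and NNAL in the same way, and match the power statement to the chosen test.

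The abstract and the Results section say analyses are complete, so naming a test now would be post hoc. The report should state which test was used, when it was chosen and whether arm results were known, and should show all three results.

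The cost is wording and a few extra analyses. The downside of the log option is that the headline becomes a ratio and depends on the detection-limit rule. Raw-scale ANCOVA is an acceptable alternative that stays in μg/m³. Any gain in power depends on the unreported baseline and should be shown as a range: with an assumed correlation of 0.3–0.7 and baseline ban share of 0–15%, simulated power was 70–89% for the raw change-score t test, 86–95% for raw ANCOVA and 98–100% for log ANCOVA.

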#### Secondary Analyses

Supportive analyses will include multivariable regressions accounting for the effect of relevant baseline sociodemographic, tobacco-related (eg, cigarettes smoked per day), and psychosocial variables (eg, depression), especially if significant effects on the outcomes or imbalance between the study groups are discovered. To utilize the repeated measures data more efficiently, we will also use linear mixed models for the continuous endpoints and the generalized linear mixed models for the binary endpoints. All regression models will include treatment, time, and possibly interactions between treatment and time, after adjusting for other aforementioned covariates. The model-based and empirical estimates of the endpoints for both treatment arms at each of the three time points will be generated and displayed with appropriate tabular and graphical methods.

#### Missing Data Analyses

We will use the intent-to-treat method to include all subjects who were randomized in the final data analysis. For subjects with missing data at week 26, a zero change score will be imputed. As a supplementary analysis, we will also use the completers-only method to analyze variables with missing values.

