### Participants

Prior to participant enrollment, all study procedures were approved by the Institutional Review Board. Participants called a designated study phone line to be screened for eligibility. All eligibility assessments were conducted over the phone, and initial eligibility status was determined immediately upon completion of the assessment.

A total of 195 participants were enrolled in this study (Figure 2). Recruitment occurred over 21 months, from June 2011 to March 2013. Final follow-up assessments were completed in August 2013. Participants were randomized to either biomarker feedback (active, n=98) or health education (control, n=97) conditions. Eligible participants were female. Although we initially allowed for enrollment of male parents/guardians, we discovered that our counselor did not feel comfortable conducting home visits with a male participant. Participants were at least 18 years of age, not planning to move out of the state over the next 3 months, willing to complete three assessments in their home over a 26-week study period, and the legal guardian of a child aged ≤10 years who lives in the home on at least 5 days of the week. In order to increase the likelihood that the home environment and the child’s urine assay would contain detectible tobacco toxins, participants were eligible if they endorsed smoking cigarettes on ≥20 days in the past 30 days, although they did not have to endorse smoking in the home. Participants were ineligible if they were pregnant, currently using any tobacco cessation aid (eg, counseling or NRT), homeless, living in a shelter or detox facility, living outside of a 30-mile radius of the university, or enrolled in a tobacco research study in the preceding 30-day period.

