#### Counselor Training

All counseling was delivered by a female study counselor who acted as the sole counselor for all participants randomized to the active condition. The study counselor received approximately 40 hours of face-to-face MAPS counseling training, followed by additional training until performance criteria for competence and adherence to the assigned protocol were reached. The counselor participated in monthly, individual supervision to maintain performance standards. In order to monitor protocol fidelity, all counseling sessions were audiotaped, a random sample of two of the counselor’s monthly sessions were coded, and detailed feedback was provided using a modified version of the Motivational Interviewing Treatment Integrity (3.1.1) [45] coding and feedback system to ensure adequate competence and adherence to the protocol.

The counselor followed a strict protocol for completion of the counseling visits and to maximize session adherence/retention. All five sessions were conducted within a 12-week window. The first, second, and fifth sessions were conducted in the participants home, and the third and fourth sessions were conducted over the telephone. The window allowed for sessions to be scheduled every other week until the end of the counseling window. Visits were scheduled at times negotiated between the participant and the counselor. The counselor made daily attempts to reach participants to schedule or reschedule a visit. In addition, contact letters were mailed to the participant’s current address and attempts were made to reach alternate contacts of persons listed by the participant, who would always know how to contact the participant.

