### Outcomes

#### Primary and Secondary Outcomes

The primary outcome for this study is change in home SHS exposure measured by the passive air nicotine dosimeter at 26 weeks poststudy enrollment. The specificity of the nicotine dosimeter as a marker of SHS is an appropriate marker to measure a reduction in home air nicotine. Reduction in child’s cotinine and NNAL levels and parental report of smoking behavior change (ie, cessation, quit attempts, reduction, and restrictions) served as secondary outcomes. Specifically, carbon monoxide–verified, 7-day, self-reported point-prevalence abstinence assessed 6 months after study enrollment and defined as no smoking, not even a puff, for 7 consecutive days prior to the final assessment point at month 6 served as the smoking cessation measure [47]. Using a conservative approach, participants who dropped out or were lost to follow-up were considered to be smoking. Adoption of home smoking restrictions was assessed by a question modified from the Current Population Survey Tobacco Use Supplement [48]: “Which statement best describes the rules about smoking in your home?” Participants reported whether there were no bans (“Smoking is permitted anywhere”), some restriction (”Smoking is allowed in some places or at some times”), or complete restriction or ban (“No one is allowed to smoke anywhere”). Smokers were also asked to report the number of cigarettes smoked per day and the number of quit attempts in at least 24 hours since enrollment and their use of programs (eg, Helpline) or pharmacological therapy (eg, nicotine replacement therapy and other cessation medications) at weeks 8 and 26.

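### Zero-change imputation at week 26 dilutes the primary difference when dropout is equal between arms and can bias it either way when dropout is unequal

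*Protocol article*

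**What the plan says.** The Outcomes section makes change in home air nicotine at 26 weeks, measured by dosimeter, the primary outcome. The Primary Analyses section tests it with a two-sided t test on the change score, with a log transformation or a Wilcoxon test if the data are not normal. The Missing Data Analyses section includes everyone randomized and fixes the rule: "For subjects with missing data at week 26, a zero change score will be imputed". It applies to both arms alike, and no reason is given for expecting no change. A completers-only analysis is supplementary. Linear mixed models over the three time points are listed under Secondary Analyses.

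The Sample Size section states: "A total sample size of 180 (90 per treatment group) was determined to achieve 85% power". The expected week-26 means are 1.15 (SD 1.58) and 1.89 (SD 1.68) μg/m³, derived from ban adoption of 55% and 25%. It mentions neither dropout nor any dilution from imputed zeros. The Results section says that enrollment and analyses are complete and interpretation is under way.

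**The concern.** An imputed zero enters the t test as if it had been measured. That is harmless only if the participants who are missing had, on average, no change. The planning model does not expect this: a quarter of control homes are assumed to have a ban at week 26, and more than half of feedback homes.

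If air nicotine falls in both arms, each imputed zero pulls its arm's mean back toward no change. With equal losses the treatment difference is diluted and the interval is centred on the wrong value. With unequal losses, the arm that keeps more participants looks better, even if treatment does nothing. The rule resembles a conservative convention but is not reliably conservative. It governs the headline result, and it sets aside an observed week-16 dosimeter value for anyone who misses only week 26.

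**Working it through.** **Inputs from the article.** Week-26 means and SDs 1.15 (1.58) and 1.89 (1.68) μg/m³; ban adoption 55% and 25%; 90 per arm planned, 98 and 97 randomized; two-sided α 0.05.

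**Assumptions.** Dropout of 10 to 30%, unrelated to outcome; no bans at baseline; SD of change as stated in each step. The article gives none of these.

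**1. Reproduce the stated power.** Pooled SD = √[(1.58² + 1.68²)/2] = 1.631. Then 0.74 / (1.631 × √(2/90)) = 3.04, and Φ(3.04 − 1.96) = 86%; the noncentral t gives 85.7%. The stated 85% holds for complete data.

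**2. Mean change implied by the planning model.** Let *a* be the mean in ban homes and *b* the mean in other homes.
- 0.55*a* + 0.45*b* = 1.15
- 0.25*a* + 0.75*b* = 1.89

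The solution is *a* = 0.04 and *b* = 2.51. With no bans at baseline, both arms start at about 2.51. The mean changes are 1.15 − 2.51 = −1.36 (feedback) and 1.89 − 2.51 = −0.62 (education).

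**3. Effect of the rule.** With missing share *m* and true mean change *c* in an arm, where subscript 1 is feedback and 0 is education:
- expected difference = (1 − *m*₁)*c*₁ − (1 − *m*₀)*c*₀
- variance in an arm = (1 − *m*)SD² + *m*(1 − *m*)*c*²

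**4. Equal dropout.** The difference becomes (1 − *m*) × 0.74. Power is by normal approximation for 98 and 97, with the SD of change taken equal to the week-26 SDs.

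| Missing, both arms | Expected difference | Power, zero rule | Power, same test on observed cases |
|---|---|---|---|
| 10% | 0.67 | 83.8% | 85.2% |
| 20% | 0.59 | 77.7% | 80.9% |
| 30% | 0.52 | 70.5% | 75.5% |

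The rule itself costs about 1 to 5 points; the rest is the missing data.

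For coverage at 15%, the bias is 0.15 × 0.74 = 0.111 and the standard error 0.222, a shift of 0.50 standard errors. Coverage is Φ(1.46) − Φ(−2.46) = 92%. At 30% the bias is 0.222 and the standard error 0.207, which gives 81%.

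A simulation of the mixture (other homes mean 2.51, SD 1.50, correlation 0.5 between baseline and week 26 in non-adopters) gives about 93% and 84%. The shift is smaller there because the SD of change is larger: √(1.50² + 0.55 × 0.45 × 2.47²) = 1.94 and √(1.50² + 0.25 × 0.75 × 2.47²) = 1.84.

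**5. Unequal dropout, planned effect present.**
- 30% missing on feedback, 10% on education: 0.70 × 1.357 − 0.90 × 0.617 = 0.39. Power is 43%, against 81% on observed cases.
- 10% on feedback, 30% on education: 0.90 × 1.357 − 0.70 × 0.617 = 0.79. The effect is overstated, and the rejection rate is 96% against 80%.

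**6. Unequal dropout, no treatment effect.** The false difference is the gap in missing share times the common mean change. That change is 0.25 × 2.467 = 0.617 with bans in 25% of homes in both arms, and 0.40 × 2.467 = 0.987 with 40%.

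| Missing | False difference (25% / 40% bans) | Type I error, simulated, raw scale |
|---|---|---|
| 10% vs 20% | 0.06 / 0.10 | about 5% / 7% |
| 10% vs 30% | 0.12 / 0.20 | about 8% / 13% |

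The normal approximation, with the SD of change set to 1.68 in both arms, gives 5.9% and 7.2% for the first row and 8.7% and 14.4% for the second. If the common change is exactly zero, type I error stays at 5%.

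**The case against.** The best defence is that assuming no change is a familiar convention for behavioural trials, that completers-only and mixed-model analyses are already planned, and that no dropout rate is given, so a harmful gap between arms is hypothetical. Part of this stands. With equal dropout, type I error is untouched. A 10-point gap raises it only to about 6%; material inflation needs a gap of about 20 points or a larger common decline. The decline also depends on few homes having bans at baseline. The Participants section did not require smoking in the home, so pre-existing bans could shrink it.

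Several stronger readings are tempting but not supported.
- **A large loss of power.** Setting the zero rule against a baseline-adjusted analysis makes the loss look large, but that changes the estimator as well. Against the same t test, the rule costs 1 to 5 points. Power is not always lost either: rejection rises when controls drop out more.
- **Regression to the mean from the entry cutoff.** The cutoff is the detection limit, 0.02 μg/m³, below even the implied ban-home mean of 0.04, so it selects very little.
- **Better retention in the feedback arm.** The statement "The counselor made daily attempts to reach participants to schedule or reschedule a visit" concerns counseling sessions, while the Retention section describes reminders for participants generally. Five sessions could also add burden. A gap is possible, but its direction is unknown.
- **The residence criterion.** "not planning to move out of the state over the next 3 months" covers less than the follow-up period, but enrollment is closed and the article does not link it to missing data.
- **Missing counted as smoking.** "participants who dropped out or were lost to follow-up were considered to be smoking" applies to the secondary cessation outcome, not to air nicotine.

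The planned alternatives soften the problem but do not remove it, because the zero-imputed test remains the primary result.

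**Conclusion.** The concern holds in this limited form. The primary missing-data rule assumes a value that the planning model expects in neither arm, provided few homes had bans at baseline. With equal dropout it understates the effect by exactly the dropout share and lowers interval coverage. With unequal dropout it can understate or overstate the effect and can produce a false one. The case rests on bias, coverage and type I error, not on power.

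The sizes are illustrative: they depend on assumed dropout rates, an assumed SD of change, and missingness unrelated to outcome. A reader might infer that the trial's result is invalid. The article does not show that, because it reports neither missingness by arm nor the observed change.

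**What to change.** - **Main estimate:** take the week-26 treatment contrast from the linear mixed model already planned, with all randomized participants who have any dosimeter value, baseline and weeks 16 and 26, and arm-by-time terms. Entry required a detectable baseline reading, so everyone randomized should contribute. Multiple imputation by arm, using baseline and week 16, is an equal alternative.
- **Sensitivity analyses:** keep zero change, labelled as such, and add a delta-adjusted tipping-point analysis.
- **Reporting:** give missingness by arm at weeks 16 and 26.
- **Disclosure:** because analyses are complete, state that the change in priority is post hoc, and show the pre-specified zero-imputed result beside the new main estimate.

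The computing cost is small. The real costs are reliance on missing at random, which the tipping-point analysis probes, and the loss of credibility that comes with reordering analyses after the data have been analysed.
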